### Intervention

Researchers will undertake a one-day training course for this trial. This course will cover the study protocol, the recording method for the clinical record form (CRF), and basic information about clinical research, a researcher's responsibility and research monitoring.

### Chemotherapy

The chemotherapy for NSCLC patients is a combination of Vinorelbine, 25 mg/m^2^, d1, 8 and DDP, 75 mg/m^2^, d1 (NP) giving three-weekly for four cycles. For patients who receive fewer than the intended number of cycles of chemotherapy, the study duration will be calculated by the basis of the projected interval.

### Chinese herbal medicine

Prescriptions formulated into granules origin from [name] in Longhua hospital. Package of granules is made into three types with functions such as benefiting Qi recipe, benefiting Yin recipe and detoxication and resolving masses recipe (Table 1). Each package contained 20 g of water-soluble herbal granules that were manufactured at a Good Manufacture Practice standard facility (Tian Jiang Ltd, Jiangyin, China). Each package was labeled with a serial number. The prescription form comprised the stock list with both the name and serial number.

**Table 1 T1:** Dosage of Chinese medicine according to different syndromes

**Syndrome Differentiation**	**Chinese Medicine (unit:package)**		
	**Benefiting Qi Recipe**	**Benefiting Yin Recipe**	**Detoxication and Resolving Masses Recipe**
Qi Deficiency	1	—	2
Yin Deficiency	—	2	2
Qi and Yin Deficiency	1	1	2
Spleen and Kidney Deficiency	2	—	2

### Placebo

It is difficult to define a pure placebo in Chinese herbal medicine where all natural substances are potentially therapeutic. So we compromise the raw materials for the placebo including 10% of Chinese medicine, food color and artificial flavors. The placebo and therapeutic packages were stored in different cabinets, and only the dispensing technician knew the contents of the packages.

### Primary outcome measurement

#### Quality of life

Quality of life scale: QLQ-LC43 scales made by EORTC will be applied to assess the quality of life of patients. Scoring method is used to assess the results according to the score changes [27]. Scores of general QOL and each field is calculated respectively by international uniform scoring system prior and after intervention. Performance status of patients physical conditions are assessed according to ECOG PS standard before and after each treatment.

### Secondary outcome assessments

Two-year disease-free survival rate: the patients without recurrence and metastasis within 2 years after resection account for percentage of all patients.

Disease-free survival (DFS) :it refers to the interval time either from the first date of medication to that of recurrence and metastasis observed, or death for any reason (record according to the first event). The date of last evaluation will be recorded if patients either have no recurrence and metastasis when reach censored data, or loss of follow-up.

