### Inclusion criteria

Meet the diagnostic criteria of primary bronchial lung cancer, and pathologically or cytologically confirmed of squamouscarcinoma, adenocarcinoma, adenosquamous carcinoma or large cell carcinoma of the lung, age between 18 and 75 years old; TCM syndromes are Yin deficiency, Qi deficiency, Qi and Yin deficiency or Spleen and Kidney deficiency, Eastern Cooperative Oncology Group (ECOG) performance status of two or less, Stage Ib ~ IIIa with complete resection, first chemotherapy treatment within 6 weeks after operation, normal hematological function with total neutrophil count >1.5 × 10^9^/l and platelets >80 × 10^9^/l, normal liver function and kidney function, voluntarily involved to clinical study and sign informed consent.

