### Sample size

Refer to the results of JRB.10 study, for early lung cancer patients after three-month adjuvant chemotherapy, the QOL score assessed by QLQ-C30 scale decreased 27% compared with baseline. The sample size of this study is based on the validity of assumptions and clinical experience of the past. Compared to the baseline, it is estimated that the QOL score assessed by QLQ-C30 scale for patients treated with three-month postoperative adjuvant chemotherapy, there was 15% of patients with no deterioration of QOL combined with TCM than treatment without TCM. Inspection level α = 0.05, grasp 1-beta = 0.90, compared with the baseline, the QOL score assessed by QLQ-C30 scale after three-months in the treatment group decline 12% while 27% in the control group, made 198 cases of sample size in each group and consider 20% off rate, it is expected that the research team observed 480 cases (n = 240 cases) of patients in 2 years to compare QOL of postoperative NSCLC patients by chemotherapy with or without TCM.

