### Statistical analysis

All the clinical data will be saved in computers after collection work and database will be set up by Microsoft Access 2007 software. Statistical analysis will be conducted on an intention-to-treat basis with a 95% confidence interval using the SPSS 16.0 statistical package. For analysis of baseline characteristics, either two-sample t tests or Wilcoxon rank sum tests for continuous data and Chi-squared tests or Fisher’s exact tests for categorical data will be conducted after the test for normality. Kaplan-Meier survival analyses should be used for calculating median survival time (MST), Long-Rank is used between two groups. A significance level of 5% will be used throughout the analysis. Experts of Shanghai Medical Clinical Research Centre will be invited to manage the statistic analysis.

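### The two-year disease-free survival rate is a raw proportion that omits death and starts from a different date than the DFS endpoint beside it

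*Protocol article*

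**What the plan says.** Secondary outcome assessments lists two related endpoints.

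- **Two-year disease-free survival rate:** "the patients without recurrence and metastasis within 2 years after resection account for percentage of all patients". The numerator is defined by absence of recurrence and metastasis, the denominator is all patients, and the clock starts at resection. Neither death nor censoring is mentioned.
- **DFS:** the time "from the first date of medication to that of recurrence and metastasis observed", "or death for any reason (record according to the first event". Patients without an event and patients lost are given their last evaluation date: "The date of last evaluation will be recorded if patients either have no recurrence and metastasis when reach censored data, or loss of follow-up".

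Statistical analysis states: "Kaplan-Meier survival analyses should be used for calculating median survival time (MST), Long-Rank is used between two groups". It names neither DFS nor the two-year rate. Inclusion criteria requires "first chemotherapy treatment within 6 weeks after operation", which limits the gap between the two starting dates.

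**The concern.** The two endpoints share a name and are both secondary aims, so a reader will expect the rate to be the DFS curve read at two years. As defined, it is not. A patient who dies at month 10 without recurrence is a failure for DFS and a success for the rate. The two results can then disagree for reasons unrelated to treatment. If deaths without recurrence are unequal between the arms, the arm with more of them looks better on the rate than it should. The starting dates also differ, and a simple proportion has no means of using partial follow-up.

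**Working it through.** The protocol gives no expected two-year rate, event count or power for DFS, so there is no figure to reproduce. The check sets the definitions side by side and then illustrates the size.

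**Definitions compared**

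| | Two-year rate | DFS |
|---|---|---|
| Death without recurrence | not an event | event |
| Time origin | resection | first medication |
| Patients lost | no rule stated | last evaluation date recorded |
| Form | proportion of all patients | time to event |

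**Assumptions (none from the document).** True two-year DFS, S, is 60% or 70%. A share d of DFS events, 5%, 10% or 20%, is deaths without recurrence. Hazards are constant and loss is independent of outcome.

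**Step 1: deaths only, nobody lost.** The rate as written is 1 − (1 − S)(1 − d), so the excess over S is (1 − S) × d.

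- S = 60%: 40 × 0.05 = 2 points, 40 × 0.10 = 4, 40 × 0.20 = 8. The rate reads 62%, 64% or 68%.
- S = 70%: 30 × 0.05 = 1.5 points, 30 × 0.10 = 3, 30 × 0.20 = 6. The rate reads 71.5%, 73% or 76%.

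**Step 2: add loss.** Let L be the probability of loss by two years in the absence of an event, taken as 20% for illustration. The share still followed and event-free is S(1 − L) = 0.60 × 0.80 = 0.48. The share with an observed DFS event is ln S / (ln S + ln(1 − L)) × (1 − 0.48) = 0.5108 / (0.5108 + 0.2231) × 0.52 = 0.362. With d = 10%, observed recurrences are 0.326 and observed deaths without recurrence 0.036.

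- Lost patients counted as disease-free: 1 − 0.326 = 67.4%.
- Lost patients counted as failures: 0.48 + 0.036 = 51.6%.

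The true value is 60%. Results at 20% loss over the full range, deaths without recurrence counted as disease-free:

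| True rate | d | Lost = disease-free | Lost = failure |
|---|---|---|---|
| 60% | 5% | 65.6% | 49.8% |
| 60% | 10% | 67.4% | 51.6% |
| 60% | 20% | 71.0% | 55.2% |
| 70% | 5% | 74.3% | 57.4% |
| 70% | 10% | 75.6% | 58.7% |
| 70% | 20% | 78.3% | 61.4% |

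Counting deaths correctly does not cure the loss problem. At 60% and 20% loss the proportion is then 63.8% or 48.0%, still on either side of the truth. Kaplan-Meier with death as an event and losses censored recovers 60% or 70% under the same assumptions.

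**Step 3: time origin.** Take first medication as the first chemotherapy, at most 6 weeks after resection. Two years from resection is then as little as 104 − 6 = 98 weeks on the DFS clock. With constant hazard and no events before first medication, 0.60^(98/104) = 61.8% and 0.70^(98/104) = 71.5%. The shift is at most about 1.8 and 1.5 points, and randomization should make it similar in both arms.

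**The case against.** The strongest defence is that this is loose wording. The endpoint's name contains survival, the DFS definition beside it includes death, and an analyst might well count a dead patient as a failure. DFS is also the only time-to-event outcome defined, so the Kaplan-Meier and log-rank sentence is sensibly read as serving DFS, with median survival time as imprecise wording. The second part stands: that sentence needs a clarifying word but is not a separate error. The first part does not remove the problem. The article states a definition, and that definition conflicts with its neighbour on both the event and the starting date. This is not detail left to an analysis plan.

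A reader might go further and infer that the plan counts lost patients as disease-free, so that the rate is certainly inflated, by about 7 points at 60%, and favours the arm with more loss. The text does not support this. It says nothing on how lost patients are classified. They stay in the denominator, and a patient last seen at month 3 is not known to have been recurrence-free for two years, so treating that patient as a failure is equally natural. Under that reading the rate is too low and the arm with more loss looks worse.

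Nor can the protocol's "consider 20% off rate" be taken as a two-year loss rate. It inflates the sample size for the three-month quality-of-life comparison. The 20% used above is only an illustration. An unstated loss rule would by itself be a matter for the full protocol or SAP. It is relevant here because the stated form, a raw proportion of all patients, leaves only choices that bias the rate.

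**Conclusion.** The point holds for death and for the time origin. As written, the two-year rate contradicts the DFS definition, and with complete follow-up the omission of death can only raise it. The excess is 2 to 8 points at a true rate of 60% and 1.5 to 6 points at 70%, if 5% to 20% of DFS events are deaths without recurrence. All these inputs are assumed.

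For losses, the conclusion is limited. The proportion is biased under either classification, and the direction is undetermined: 67.4% or 51.6% against a true 60%, with 20% loss and 10% of events deaths. A claim of net overstatement once losses are included would go beyond the document.

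This should be fixed, but it concerns a secondary endpoint with no power calculation attached and does not touch the primary quality-of-life analysis.

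**What to change.** Define the two-year DFS rate as the Kaplan-Meier estimate at 24 months of the DFS endpoint. Use the same events (recurrence, metastasis, death from any cause), one stated time origin for both measures, and the same censoring at last evaluation. Report the between-arm difference with a 95% confidence interval: the difference of the two estimates ± 1.96 × the square root of the sum of their Greenwood variances. In Statistical analysis, name DFS as the endpoint for the Kaplan-Meier and log-rank analysis.

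The cost is a few sentences and no new data, since DFS already needs the event and last-evaluation dates. The reported rate falls where deaths had been counted as disease-free. For losses it may move either way, depending on how they would have been classified.

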**Methods and design:**

This study is a multi-center, randomized, placebo-controlled, double-blind trial. Four hundred eighty patients will be recruited into seven different research centers in China. These patients that meet the inclusion criteria will be randomized into either a treatment group or a placebo group. Each group will receive treatments of 3-weekly chemotherapy with TCM or placebo for four cycles. The primary outcome will involve the evaluation of QOL and the secondary outcome assessments will include two-year disease-free survival rate and disease-free survival. Other efficacy assessments are changes of TCM symptoms and toxicity. Side effects and safety profile of the therapy would be evaluated at the same time. The investigators expect that TCM therapy combined with chemotherapy is superior to chemotherapy solely in terms of QOL improvement and disease-free survival extension. "Intention-to-treat" analysis will include all randomized participants.

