### Study aims

The primary aim of this study is to evaluate the effectiveness of chemotherapy combined with or without TCM in QOL of postoperative NSCLC patients. The secondary aims are to compare the disease-free survival time (DFS), two-year disease-free survival rate and safety of intervention in the two groups.

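### DFS and the two-year DFS rate have different time origins and event lists, and the DFS origin is undefined for patients randomised but never medicated, which conflicts with the stated intention-to-treat analysis

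*Protocol article*

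**What the plan says.** The Study aims section makes both endpoints comparative: "The secondary aims are to compare the disease-free survival time (DFS), two-year disease-free survival rate and safety of intervention in the two groups".

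Secondary outcome assessments then defines each one.

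- **Two-year DFS rate:** "the patients without recurrence and metastasis within 2 years after resection account for percentage of all patients". The origin is resection, the events named are recurrence and metastasis, and the summary is a plain percentage.
- **DFS:** "it refers to the interval time either from the first date of medication to that of recurrence and metastasis observed". The origin is first medication. A further clause adds death to the events: "or death for any reason (record according to the first event".

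On the analysis population, the abstract (Methods and design) says that the intention-to-treat "analysis will include all randomized participants". The Statistical analysis section repeats the commitment: "Statistical analysis will be conducted on an intention-to-treat basis". That section also names Kaplan-Meier estimation and a log-rank comparison.

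Inclusion criteria limit the gap between surgery and treatment: "first chemotherapy treatment within 6 weeks after operation". Neither endpoint definition mentions randomisation.

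**The concern.** Two endpoints that share a name would normally be two summaries of one time-to-event variable. Here they are different variables. A reader who compares the reported two-year rate with the DFS curve at 24 months will find two numbers that need not agree and were not designed to.

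The more important issue is the DFS origin. An intention-to-treat comparison needs a start time that exists for every randomised patient. First medication is itself an event after randomisation. If it never happens, the definition gives the patient no DFS value. If the disease recurs or the patient dies before it happens, the event precedes the clock. The analyst must then either leave out such patients, against the stated population, or supply an origin that the definition does not contain.

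This matters because the abstract says the investigators expect the combination to be superior on extension of disease-free survival. An endpoint meant to carry that claim should keep the full protection of randomisation.

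**Working it through.** The article gives no event count, hazard ratio, expected DFS rate or power for DFS, so there is no figure of the plan's own to reproduce. The check compares the definitions and then gauges the size.

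**1. The definitions side by side**

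| | DFS | Two-year DFS rate |
|---|---|---|
| Origin | First medication | Resection |
| Events | Recurrence, metastasis, death from any cause | Recurrence and metastasis |
| Summary | Time to event, censored at last evaluation | Percentage of all patients |
| Exists for every randomised patient? | No: needs a first dose | Yes: complete resection is an entry criterion |

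A patient who dies without recurrence in the second year is a DFS event but, read literally, is not a failure for the two-year rate. A common origin alone would therefore not reconcile the two.

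**2. Order of the dates**

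Complete resection is an entry criterion, so resection comes before randomisation. Study design has participants allocated and then treated, and the exclusion criteria rule out patients with prior or current chemotherapy. The order is resection, randomisation, first medication. The DFS clock starts after randomisation and leaves a gap in which events can occur.

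**3. Size of the difference in origin**

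- Maximum gap: 6 weeks = 42 days, or 42 / 30.4375 = 1.38 months. This holds only if medication means chemotherapy; the text does not say whether it means that or the study granules.
- Assumptions, none given in the article: constant hazard from first medication, no event before it, and a proportion *S* of 50% to 80% disease-free 24 months after it.
- Formula: h = −ln(*S*) / 24. Two years after resection is 24 − m months after first medication, so the resection-based rate is exp(−h(24 − m)). To isolate the origin, the same events are used for both.

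| *S* at 24 months from medication | m = 2 weeks (0.46 months) | m = 6 weeks (1.38 months) |
|---|---|---|
| 0.50 | 0.5067 (+0.7 points) | 0.5203 (+2.0 points) |
| 0.60 | 0.6059 (+0.6) | 0.6179 (+1.8) |
| 0.70 | 0.7048 (+0.5) | 0.7145 (+1.5) |
| 0.80 | 0.8034 (+0.3) | 0.8103 (+1.0) |

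The resection-based figure is higher by 0.3 to 0.7 points at 2 weeks and by 1.0 to 2.0 points at 6 weeks. The shift applies to both arms.

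**4. Patients without a DFS start date**

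The share who never start is not stated. At an assumed 1%, 0.01 × 480 = 4.8, about 5 patients. At an assumed 5%, 0.05 × 480 = 24 patients.

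**The case against.** Four points can be made for the plan.

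- **No passage excludes non-starters.** A reader might infer that the DFS analysis is not intention-to-treat and that untreated patients will be dropped. The documents do not go that far: they promise the opposite, and a fuller protocol or SAP could set a rule for these patients. This stands as a limit on the claim. It does not remove the conflict, because the definition as printed cannot be applied to everyone the analysis is said to include. A later rule would have to override it.
- **The offset is small and common to both arms.** This stands. Six weeks is 42 / 730 = 5.8% of the two-year window, but that is a share of time and a maximum, not an effect on the result. Both arms receive chemotherapy with granules or placebo under double blinding, so there is little reason to expect the gap, or failure to start, to depend on arm.
- **The two-year rate is not affected by non-starters.** This stands. Its origin exists for every eligible patient and its denominator is all patients.
- **The number of non-starters is unknown.** This stands. The range of 5 to 24 is an illustration.

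A reader might also infer that the whole interval from resection to chemotherapy is free of events by design. It is not: once a patient is randomised, recurrence or death can occur before the first dose.

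**Conclusion.** The point holds as an inconsistency in stated definitions, not as a detail left to another document. DFS and the two-year DFS rate differ in origin and in event list, so the rate is not a reading of the DFS curve. The DFS origin lies after randomisation and is undefined for patients never medicated, which cannot be squared with the stated analysis population.

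The consequences are modest. The difference in origin is worth at most about 1 to 2 points under the assumed hazard and rates, and does not by itself bias the comparison between arms. The possible loss of non-starters, and of events before the first dose, matters more in principle, but its size rests on an assumed share. The effect of leaving death out of the two-year rate cannot be sized, because the article gives no rate of death without recurrence. Both endpoints are secondary, and the only sample size calculation is for quality of life. The change should be made, but the primary analysis does not depend on it.

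**What to change.** Rewrite the two definitions under Secondary outcome assessments:

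1. DFS runs from the date of randomisation, for every randomised patient, to the first of recurrence, metastasis or death from any cause, and is otherwise censored at the last evaluation.
2. The two-year DFS rate is the Kaplan-Meier estimate of that same variable at 24 months, by arm.
3. Any figure timed from resection is descriptive only.

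All three parts are needed, since moving the origin alone would leave the event lists and the type of summary different.

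The cost is a few sentences. The article does not say that the randomisation date is recorded, but computer-generated allocation makes this a reasonable expectation. Follow-up to 24 months from randomisation ends later than two years from resection, by no more than the 6-week gap for patients who start chemotherapy on time. The one real downside is slightly less direct comparability with published figures timed from surgery, which the descriptive figure covers.

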### Other outcome assessments

#### Evaluation of TCM symptoms changes

The symptoms scores are made, recorded and calculated based on graded scale of lung cancer symptoms required in "The Guiding Principles of Clinical Research of New Chinese Medicine treating Primary Bronchial Lung Cancer" (2002) issued by the State Drug Administration before and after each treatment. The total scores of single symptom are TCM symptoms scores, and symptoms efficacy assessments are based on the changes before and after treatment.

### Safety assessment

Blood routine, liver and kidney function, urination and stool routine and EKG will be measured before and after treatment to assess the toxicity and side effects of each group according to Common Terminology Criteria for Adverse Events V3.0 (CTC AE) issued by National Cancer Institute (NCI) (http://ctep.cancer.gov/).

AEs is recorded according to Common Terminology Criteria for Adverse Events V3.0 (CTC AE) made by National Cancer Institute (NCI) (http://ctep.cancer.gov/) after treatment each week.

